### Sample size

The sample size calculation is based on changes in lifestyle behaviors and health outcomes, for which we used data from a previous study on inpatients in the Netherlands [19]. A sample size of 98 participants is necessary to detect an average effect (f^2^ = 0.15) in a linear regression analysis with 80% power, 95% confidence interval, and six variables in the model. After reaching consensus on feasibility with the collaborating region, it was decided to enroll 50 people to participate in the GOAL! program and recruit an equally sized control group.

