Participants’ personal information will only be used for measurement purposes and to share general study results, as specified in the consent form. The data will be pseudonymized, personal information will be stored separately, and both will be accessible only to the research team. Access to the data requires two-factor authentication. Data is stored within the institution for 15 years, following national privacy laws, and will not be publicly released.

If participants in the GOAL! program decide to withdraw, they will be asked to remain in the evaluation for additional analysis. If participants withdraw their consent for the evaluation, any data collected prior to withdrawal will be stored in accordance with the data protocol and Dutch law but will not be used for analysis or publication.

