### Statistical analysis

To assess the effect of GOAL! on lifestyle behaviors and health outcomes, data will be analyzed via multiple linear regressions and linear mixed models (LMMs). LMMs allow for testing the effect over time (four measurement points) and accounting for potential clustering (e.g., participant groups). In all analyses, the treatment condition (GOAL! participants vs. control group, coded as 1/0) will be the independent variable, and the outcomes measures will be the dependent variables, with physical activity (in minutes per week) as the primary outcome. All analyses will be adjusted for potential confounders, such as age (continuous), sex (male vs. female, coded as 0/1), key diagnostic subgroups (categorial, added as dummy variables), baseline values (continuous), session adherence (continuous), and changes in medication use (continuous).

When necessary, missing data will be addressed through multiple imputations via the MICE package in R. When constructing the imputation model, we will include the variables used as predictors in our analysis. The number of imputations and iterations will be based on the proportion of missing data in our LMM. Results from imputed datasets will be pooled using Rubin’s rules.

Implementation factors are processed according to the manual of the measurement instrument. Cost-effectiveness is analyzed in a health-technology assessment.

All analyses will be performed with IBM SPSS statistics 25 and R version 4.04 or higher, based on 95% confidence intervals (*p* < 0.05), and if necessary will be corrected for multiple outcomes (Bonferroni correction).

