Several limitations should be considered within the protocol of this study. First, it is challenging to include people with SMI in intervention research because of illness and healthcare-related complexities. People with SMI often face motivational barriers, self-stigma, psychological complaints, or medication side effects, potentially leading to low enrollment, low adherence, and high dropout rates [33, 34, 66]. Furthermore, healthcare practitioners may encounter inconsistencies in defining who meets the criteria for severe mental illness, organizational barriers (e.g., changes in work practices), and stigma (e.g., negative beliefs and attitudes towards people with SMI, leading to the exclusion of potential participants) [67, 68], which can lead to selection bias.

Second, participants are asked to answer many questions at each measurement point, which can be perceived as burdensome. Some questionnaires may also be difficult to answer or may include sensitive topics. To address these issues, questions can be answered face-to-face or via an online questionnaire, measurements can be spread over multiple sessions, and participants are allowed to skip questions.

Third, for GOAL! participants, half of the questionnaires are administered by the lifestyle coach and the other half by the research team, leading to variability in the data for the outcome measures. However, this is minimized by using as many validated instruments as possible and standardizing measurements and training and consultation throughout the process.

Lastly, the implementation of GOAL! takes place in a select region of the Netherlands, which may limit the generalizability of the findings. In addition, because the control group is recruited in other regions, various contextual factors may influence outcomes. However, this approach helps prevent contamination, and by evaluating the implementation and considering these contextual factors, we aim to gain insights into context-specific barriers, facilitators and processes. This understanding will assist in the interpretation of the outcomes and potential implementation of GOAL! in other regions.

The results of this study will provide a comprehensive understanding of the effectiveness and implementation of GOAL!, serving as essential input for informed decision-making regarding the future integration of lifestyle interventions into outpatient care for people with SMI.

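### Enrolling 100 against 98 stated as necessary leaves a margin of two, with no allowance for attrition or clustering, and the test behind the 98 is not named

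*Protocol article*

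**What the plan says.** All references are to the protocol article.

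- **Sample size.** "A sample size of 98 participants is necessary to detect an average effect (f^2^ = 0.15"), and this is "in a linear regression analysis with 80% power, 95% confidence interval, and six variables in the model". The section does not say which hypothesis is tested, the whole model or the treatment term. After agreement on feasibility with the region, "it was decided to enroll 50 people to participate in the GOAL! program and recruit an equally sized control group". No attrition rate and no design effect are given.
- **Design and setting.** Measurements run to 24 months, at four time points.
- **Discussion, limitations.** Barriers in this population are described as "potentially leading to low enrollment, low adherence, and high dropout rates". No rate is given.
- **Data collection and management.** People who leave the program are asked to stay in the evaluation. If consent for the evaluation is withdrawn, data already collected are stored "but will not be used for analysis or publication".
- **Statistical analysis.** Linear mixed models are planned, partly for "accounting for potential clustering (e.g., participant groups"), with multiple imputation when necessary. No group size or intraclass correlation (ICC) is stated.

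**The concern.** A number required for a given power is a number analysed. If 98 must be analysed and 100 are enrolled, the power statement tolerates a 2% loss over two years, in a population for which the article itself warns of dropout. The calculation also treats observations as independent, although the intervention is delivered largely in groups and the analysis section allows for clustering.

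At stake is how the result is read. Someone who takes 100 enrolled as satisfying 98 will judge a non-significant finding against a nominal 80% power that the stated calculation supports only with almost complete data. Because the article does not say which test the 98 serves, the reader also cannot tell what power the trial has for its primary comparison.

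**Working it through.** **Inputs from the article:** f² = 0.15, α = 0.05, k = 6 variables, target power 80%, 98 necessary, 50 + 50 enrolled. **Assumed, because the article gives no figures:** loss of 10%, 20% or 30%; GOAL! groups of 10; ICC 0.05 (range 0.02 to 0.10), in the GOAL! arm only.

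**1. Reproduce 98.** Power = P(F′ > F_crit), where F′ is noncentral F with u numerator df, v = N − k − 1 denominator df and λ = f²·N. For the overall test, u = 6. At N = 98: v = 91, λ = 0.15 × 98 = 14.7, F_crit = 2.20, power 80.4%. At N = 97: v = 90, λ = 14.55, power 79.8%. So 98 is the smallest N that reaches 80%, an exact match with no inflation built in. The alternatives do not give 98: testing one coefficient among six predictors needs 55, two need 68 and three need 77. The overall test with five predictors needs 92, and with seven 103.

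**2. Loss, same overall test.** Each lost participant is counted as contributing nothing.

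| Analysed | Loss from 100 | Power |
|---|---|---|
| 100 | 0% | 81.3% |
| 98 | 2% | 80.4% |
| 97 | 3% | 79.8% |
| 90 | 10% | 76.0% |
| 80 | 20% | 69.5% |
| 70 | 30% | 61.8% |

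**3. The treatment coefficient (u = 1, k = 6).** Solve for the f² that gives 80% power at each N. With equal arms, and treatment uncorrelated with the other covariates, d = 2√f², in residual SD units. For clustering in one arm, the design effect is 1 + (10 − 1) × 0.05 = 1.45. The variance of the contrast rises by (1.45 + 1)/2 = 1.225, so the detectable d rises by √1.225 = 1.107.

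| Analysed | Detectable d | With assumed clustering (× 1.107) |
|---|---|---|
| 100 | 0.566 | 0.63 |
| 90 | 0.598 | 0.66 |
| 80 | 0.635 | 0.70 |
| 70 | 0.680 | 0.75 |

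Over ICC 0.02 to 0.10 the multiplier runs from √1.09 = 1.04 to √1.45 = 1.20.

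**4. Compare with the stated effect.** If f² = 0.15 is the treatment's own partial effect, d = 2√0.15 = 0.775. Every detectable effect in the second table is smaller. Power for that effect is 96.9% at 100 analysed, 92.8% at 80 and 89.1% at 70. At 70 with the assumed clustering it is about 82%. At 70 with ICC 0.10 it drops to about 75%, where the detectable d is 0.680 × 1.204 = 0.82.

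**The case against.** The strongest reply is that the primary question is GOAL! against usual care, which is one coefficient. If f² = 0.15 belongs to it, 55 analysed are enough and 100 enrolled tolerates a 45% loss. This stands as arithmetic. It rules out the inference, which a reader might draw, that the trial will fail to deliver 80% power for its primary comparison. It does not rescue the stated figure, because the calculation that yields 98 is not that test, and the article nowhere assigns f² = 0.15 to the treatment.

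Other stronger readings are also unsupported:

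- A reader might infer that the article expects high dropout. It names dropout as a possibility and gives no rate.
- A reader might infer that the data of everyone who drops out are deleted. They are stored, and left out of the analysis only when evaluation consent is withdrawn. People who leave only the program are asked to stay.
- A reader might treat clustering as an established cost. The article calls it potential and gives nothing from which to size it.

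Mixed models over four time points, with imputation, recover some information from partly observed participants, and the vouchers rise at each assessment, which should help retention. The attrition cost in step 2 is therefore an upper bound at each loss rate. Neither method recovers people excluded after withdrawing consent. The article also does not fix 24 months as the primary time point, so the number analysed depends on which time point is meant.

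Finally, a full protocol or analysis plan may say more. It could hardly contain an unseen allowance within these two numbers, however: 98 reproduces exactly without one, and enrolment is fixed at 100.

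**Conclusion.** The point holds in limited form. The figure of 98 is correctly calculated for the overall six-predictor test, but 100 enrolled exceeds it by only two, with nothing stated for attrition or clustering. On that calculation the 80% is lost with the third participant, and power is 76%, 69% and 62% at 10%, 20% and 30% loss. Those rates are assumptions, and the figures count every loss as complete.

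The shortfall belongs to the test behind 98. It is not shown for the treatment effect: the detectable d stays below 0.775 throughout the assumed loss range, including with ICC 0.05 in groups of 10. It passes 0.775 only in harsher combinations, such as 30% loss with ICC 0.10. Which description applies to the primary comparison depends on what f² = 0.15 refers to, and the article leaves that open.

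**What to change.** Rewrite the power statement in the Sample size section; no extra recruitment is proposed.

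1. Say which test the 98 refers to, and whether f² = 0.15 is the whole model or the treatment term.
2. State the assumed loss, and the assumed group size and ICC, with reasons.
3. Restate power, or the detectable treatment effect, at the expected number analysed and the time point meant.
4. Do not present 100 enrolled as meeting a requirement of 98 analysed.

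Possible wording, to be completed with the sponsor's own assumptions: *The figure of 98 is for the overall test of a six-predictor regression and assumes complete, independent data. For the coefficient comparing GOAL! with usual care, if 70 to 80 of 100 participants are analysed, the effect detectable with 80% power is d of about 0.68 to 0.635, or about 0.75 to 0.70 with an ICC of 0.05 in GOAL! groups of 10. If f² = 0.15 is the treatment's own effect, it corresponds to d of about 0.77.*

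The cost is one paragraph. The stated power for the overall test becomes less favourable, while the position for the treatment comparison becomes clearer and may look better than the present text suggests.

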### Intervention

GOAL! provides multidisciplinary support from registered allied health professionals and peer support workers. In a two-year program, participants receive group-based and individual support on different lifestyle behaviors. The program is divided into the guidance phase (first year), and the maintenance phase (second year) (Fig. 1).

The program starts with an intake session of 60 min conducted by the lifestyle coach, during which lifestyle behaviors, health outcomes, and individual needs are examined. Lifestyle goals are set through shared decision making, a collaborative process proven to enhance effectiveness [42]. In the guidance phase (i.e., year one), the program starts with a 3-month basic course, which encompasses 36 group sessions, each lasting 60 min, guided by allied health professionals. This includes 2-weekly sessions on physical activity (24 sessions in total) and 1-weekly session on nutrition (12 sessions in total). To achieve sustainable lifestyle behavioral change, there is a close collaboration with local stakeholders, thereby facilitating a transfer to the community setting. Thereafter, the aftercare of 9 months starts, with a thematic session of 60 min every two weeks (18 sessions in total) guided by the lifestyle coach about other lifestyle-related topics. These themes can vary based on the needs of the group and include themes such as smoking, sleep, and stress. In the guidance phase, participants receive 8 h of individual support from the lifestyle coach. This coaching can be utilized at the discretion of the participant and is centered around their self-identified lifestyle goals. As the participants’ options, needs and goals evolve, the coaching is adjusted accordingly. Group and individual sessions include theoretical education, interactive elements, assignments, physical activity, and supplementary practical activities (e.g., supermarket visits).

During the maintenance phase (i.e., second year), there are 3 group sessions of 90 min each, and 5 moments of individual support of 30 min each, both guided by the lifestyle coach. Participants are encouraged to continue their activities in the community setting while the lifestyle coach has a key role in communication and connection with community partners as needed. Following each phase, lifestyle coaches assess and evaluate the changes in lifestyle behaviors and health outcomes together with the participants, setting new goals accordingly through shared-decision making.

**Fig. 1 Fig1:**
[figure not shown]
Design of the GOAL! intervention

### Outcome measures

The primary outcome is the change in physical activity between participants of GOAL!, compared to participants who receive care as usual. Secondary outcomes focus on changes in other lifestyle behaviors, physical health, mental well-being, and healthcare and social costs. In addition, the achievement of lifestyle goals, adverse effects, and barriers and facilitators to implementation are examined. Implementation factors are also investigated among healthcare practitioners and stakeholders.

### Measurements

#### Demographic characteristics

At baseline, all participants are asked about their personal characteristics, including gender, nationality, ethnicity, date of birth (for age calculation), marital status, highest level of education, primary source of income, and income level. The diagnosis is obtained from patient records to ensure reliability.

#### Lifestyle behaviors

##### Physical activity and sedentary behavior

The Simple Physical Activity Questionnaire (SIMPAQ) is used to assess physical activity and sedentary behavior. The SIMPAQ consists of 5 items (boxes), averaged over the past 7-day period: time spent in bed overnight (box 1), time sedentary, including napping (box 2), time spent walking (box 3), time spent exercising (box 4) and time spent in incidental activity (box 5). The time spent walking and exercising (boxes 3 and 4) will be combined to calculate the total self-reported moderate-vigorous physical activity time, in hours per week. Alternatively calculating sedentary behavior in hours per day is advised, by subtracting the total non-sedentary behavior (adding boxes 1,3,4 and 5) from 24 h. The SIMPAQ is a reliable and valid tool for assessing physical activity and sedentary behavior in people with SMI [43].

##### Eating behavior

Eating behavior is measured through a Dutch online tool called ‘MijnEetmeter’, a food diary offered on the website of The Nutrition Center of the Netherlands [44]. The relative validity of MijnEetmeter is similar to that of other self-administered apps, although there appears to be more underreporting compared to interviewer-administered 24-h recalls [45]. We chose MijnEetmeter because of its usability for both practical and research purposes. This free tool includes nearly all Dutch food products, enabling users to log their nutritional intake. It calculates daily nutrient intake and consumption of food groups according to the Dutch ‘Wheel of Five’ dietary guidelines [46]. MijnEetmeter provides comprehensive insights into dietary patterns for participants and professionals, facilitating nutritional coaching. Additionally, it offers feedback on dietary behavior, fostering self-management. The tool was initially used in nutrition sessions, but was not found to be sufficiently user-friendly for participants, leading to its discontinuation for practical purposes and its exclusive use for research. The participants were asked to report their dietary intake for the previous day.

##### Sleep

The Scales for Outcomes in Parkinson’s disease sleep (SCOPA-sleep) is used to assess sleep. The SCOPA-sleep examines total scores for nighttime sleep quality (5 items) answered on 4-point Likert scales ranging from 0 (not at all) to 4 (heavily). In addition, the measurement assesses daytime sleepiness (6 items) from never (0) to often (4) [47]. The SCOPA-sleep is a reliable and valid instrument for assessing nighttime and daytime sleep in people with mental disorders [48].

##### Substance use

Substance use is assessed by the Alcohol, Smoking, and Substance Involvement Screening Test Lite (ASSIST-Lite). The ASSIST-Lite examines total scores for the use, frequency, urges, control and worries about the use of tobacco, alcohol, cannabis, stimulants, sedatives, opioids, and psychoactive substances. Questions are asked via Likert scales ranging from 0 (never) to 4 (multiple times a week or daily), and ordinal scales ranging from 0 (no) to 1 (yes). The instrument has been adapted and recognized for use in health and social care settings [49]. Items about tobacco smoking are additionally added to retrospectively calculate the packs per year [50].

#### Physical health outcomes

Weight (kg) and body fat percentage are measured by the Omron BF214 scale [51], with participants wearing clothes but without shoes. Length (m) is requested from the participant and BMI (kg/m²) is calculated. Blood pressure (mmHg) is measured by the Omron M7 Intelli IT blood pressure monitor [52]. The waist circumference (cm) is measured by the SECA 201 [53] measuring tape at the level of the navel in a standing position.

#### Mental health outcomes

##### Psychiatric symptoms

The Brief Symptom Inventory (BSI) is used to assess psychiatric symptoms. The BSI consists of 53 items covering 9 symptom domains of the SCL-90-R, examining scores for 9 symptom dimensions: somatization, obsession-compulsion, interpersonal sensitivity, depression, anxiety, hostility, phobic anxiety, paranoid ideation, and psychoticism. Each item is assessed via a 5-point Likert scale, ranging from 0 (not at all) to 4 (extremely) [54]. The BSI is reliable and its validity is supported across patient groups with various diagnoses in a Dutch sample [55].

##### Quality of life

The Euro-Qol-5D-3 L (EQ-5D-3 L) is used to measure quality of life. The EQ-5D-3 L measures health-related quality of life in 5 dimensions of health: mobility, self-care, daily activities, pain/discomfort, and anxiety/depression, with one item per dimension, scored from 1 (no problems) to 3 (many problems). The Dutch tariff will be used to estimate the index score based on the preferences of the Dutch population [56]. Moreover, participants are asked to indicate their overall health on the day of questionnaire completion on a scale of 0-100, the Visual Analogue Scale [57]. The EQ-5D-3 L is considered a valid instrument for assessing people with SMI [58].

#### Healthcare and societal costs

The Treatment Inventory of Costs in Patients with psychiatric disorders (TIC-P) is used for the evaluation of healthcare utilization, medication use, and productivity loss due to health problems. The TIC-P consists of 14 questions to assess healthcare utilization in the past 3 months (e.g., doctor visits, treatment, and medication use), and 11 questions about productivity losses due to health problems (e.g., hindering paid and unpaid work). The costs are calculated by multiplying the quantity of healthcare utilization and productivity loss by the related costs according to national guidelines. The TIC-P is a feasible and reliable instrument for people with mental health problems [59].

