#### Cost-effectiveness

The cost-effectiveness of GOAL! is determined through a Health Technology Assessment (HTA), using the outcomes of the TIC-P. To weigh the costs against health-related outcomes, the main outcome is the deterministic incremental cost-effectiveness ratio using the EQ-5D-3 L scores, resulting in the quality-adjusted life years (QALY). For further evaluation, we perform probabilistic sensitivity analyses to account for the uncertainty surrounding the parameters, resulting in cost-effectiveness planes. The QALY is the most commonly used outcome in the economic evaluation of medical interventions and captures the impact of GOAL! on both the quantity and quality of life [61].

**Table 1 Tab1:** Overview of assessment procedures, measurements and variables

Assessment points	Outcome measures	Measurements	Variables	Lifestyle coaches	Research team	

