**Intervention and control group**						
T0	Demographic characteristics	Gender	Categorical		x	
		Nationality	-		x	
		Ethnicity	Categorical		x	
		Date of birth (age)	Years		x	
		Diagnosis	Categorical		x	
		Marital status	Categorical		x	
		Highest level of education	Categorical		x	
		Primary source of income	Ratio		x	
T0, T1, T2, T3	Physical activity and sedentary behavior	Simple Physical Activity Questionnaire (SIMPAQ)	Moderate-vigorous physical activity in min/week and sedentary time per day	x		
	Eating behavior	MijnEetmeter	Daily intake of nutrients and daily consumption according to the Dutch ’Wheel of Five’		x	
	Sleep	Scales for Outcomes in Parkinson’s Disease sleep (SCOPA-sleep)	Total scores for nighttime sleep quality and daytime sleepiness	x		
	Substance use	Alcohol, Smoking and Substance Involvement Screening Test Lite (ASSIST-Lite)	Total scores of tobacco, alcohol, cannabis, stimulants, sedatives and opioids and psychoactive use	x		
	Physical health	Weight	kg	x		
		Abdominal circumference	cm	x		
		BMI	kg/m^2^	x		
		Fat percentage	%	x		
		Blood pressure	mmHg	x		
	Psychiatric symptoms	Brief Symptom Inventory (BSI)	Total scores for 9 symptom dimensions: somatization, obsession-compulsion, interpersonal sensitivity, depression, anxiety, hostility, phobic anxiety, paranoid ideation and psychoticism		x	
	Quality of life	Euro-Qol-5D-3 L (EQ-5D-3 L)	Index score based on the Dutch tariff and VAS score		x	
T0, T3	Care and social costs	Treatment Inventory of Costs in Patients with psychiatric disorders (TIC-P)	Healthcare utilization, medication use, productivity loss and costs (€)		x	

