### Data collection and management

All participants receive study information through a visual informed consent, using visual elements to explain the procedures, risks, and benefits of study participation, thereby enhancing understanding and communication. Additionally, they receive a written information letter, after which they are requested to provide permission by signing an informed consent form. Measurements are taken through semi-structured interviews, physical measurements, and online questionnaires at start (T0), and after 3 (T1), 12 (T2) and 24 months (T3).

For GOAL! participants, data collection will be conducted by the lifestyle coach and the research team. As this research follows innovative care, lifestyle coaches assess lifestyle behavior, physical health outcomes, and lifestyle goals at all four assessment points (T0-T3). This is part of the program but will also be utilized for research purposes. Lifestyle coaches will record examination results on hard-copy documents, which will then be transferred and securely stored by the research team. Trained researchers and research assistants administer additional questionnaires and measurements. These include psychiatric symptoms, quality of life, and eating behavior at all four assessment points (T0-T3), and healthcare utilization, somatic illness, work, and the implementation process only at the start and end of the program (T0 and T3). Research assistants undergo structured training by experienced research team members in conducting semi-structured interviews via research and interview protocols.

The research team collects all data from the control group. Lifestyle behaviors, physical health outcomes, psychiatric symptoms, and quality of life are evaluated at all four assessment points (T0-T3), whereas healthcare utilization, somatic illness, and work are evaluated only at the start and end of study participation (T0 and T3).

All surveys in this study are entered in, and facilitated by Castor EDC, a cloud-based research data management platform [62]. At T1 and T2, participants have the option to complete some questionnaires via an online survey, thus shortening or obviating the need for an interview with the research team (Table 1). Furthermore, healthcare practitioners and stakeholders receive an online survey regarding the implementation process at the start and the end of the program (T0 and T3). Their informed consent is obtained online.

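### Healthcare use is observed for only 3 of the 24 months after start, and never in the intensive first year, which cannot support an observed two-year cost-effectiveness ratio

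*Protocol article*

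**What the plan says.** Under Healthcare and societal costs, the protocol article states: "The TIC-P consists of 14 questions to assess healthcare utilization in the past 3 months". The same section adds "11 questions about productivity losses due to health problems", without a recall period for them. Costs are quantities multiplied by national unit costs.

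Table 1 schedules the TIC-P at T0 and T3. Data collection and management confirms this for each arm. For controls, "healthcare utilization, somatic illness, and work are evaluated only at the start and end of study participation (T0 and T3"); for GOAL! participants, these items are collected "only at the start and end of the program (T0 and T3"). Design and setting puts T0 at the start and T3 at 24 months.

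Under Cost-effectiveness, the economic result "is determined through a Health Technology Assessment (HTA), using the outcomes of the TIC-P", and "the main outcome is the deterministic incremental cost-effectiveness ratio using the EQ-5D-3 L scores", expressed per QALY. The EQ-5D-3L is taken at T0, T1, T2 and T3. The Discussion paragraph of the abstract gives the horizon as two years. Process evaluation says that attendance, coaching use and dropout are recorded throughout, but does not link these records to costs.

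**The concern.** A two-year incremental cost-effectiveness ratio needs costs and effects over the same two years. Here the effect side has four measurements across the period. The healthcare cost side has one look back before the programme and one at its end. Year 1 holds the basic course, the aftercare and most of the coaching, so it is where a change in care use or an admission would matter most, and it is not measured. The Background itself describes higher healthcare use and hospitalisation risk in this population.

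A second question is whether the programme's own cost is captured. Controls do not receive GOAL!, so its delivery cost is a certain difference between the arms. The only cost instrument named looks back from month 24, when little of the programme remains to be delivered.

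Cost-effectiveness is part of the stated aim. A later analysis plan can choose an extrapolation rule, but it cannot recover data that were never collected.

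**Working it through.** The article gives no coverage figure to reproduce, so the check is arithmetic on its own schedule.

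**Recall windows for healthcare use** (3 months; T0 = month 0, T3 = month 24)
- T0 window: months −3 to 0, before the programme.
- T3 window: months 21 to 24.
- Observed after start: 3/24 = 12.5%. Unobserved: 21/24 = 87.5%.
- Observed in year 1: 0 of 12 months. Observed in year 2: 3 of 12.

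**What extrapolation could do.** No rule is stated, so two simple ones serve as illustration. Let C0 and C3 be the 3-month costs reported at T0 and T3; 24 months hold 24/3 = 8 such periods.
- Carrying the last window back: 8 × C3.
- Linear interpolation, treating each window as the rate at its assessment time: 8 × (C0 + C3)/2 = 4·C0 + 4·C3.

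Neither contains any information from months 0 to 21. Interpolation gives half its weight to a period before the programme. A rise or fall in year 1 that has gone by month 21 leaves no trace.

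**Scheduled programme contact per participant** (Intervention section)
- Year 1: intake 1 h + basic course 36 × 1 h + aftercare 18 × 1 h + individual coaching 8 h = 63 h.
- Year 2: 3 × 1.5 h + 5 × 0.5 h = 4.5 + 2.5 = 7 h.
- Total: 70 h.
- Inside the T3 window: at most 7/70 = 10%, if every year-2 contact fell in the last 3 months. With an even spread over year 2 (assumption), 7 × 3/12 = 1.75 h, or 1.75/70 = 2.5%.
- Outside the T3 window: at least 63/70 = 90%; 97.5% with an even spread.

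**From participant hours towards cost.** A group hour is shared, so divide group hours by an assumed group size g. Professional hours per participant are 1 + 8 + 2.5 + (36 + 18 + 4.5)/g = 11.5 + 58.5/g. The year-2 part is 2.5 + 4.5/g.

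| Assumed g | Total h | Year-2 h | Most that can lie in T3 window | Even spread |
|---|---|---|---|---|
| 5 | 23.2 | 3.4 | 14.7% | 3.7% |
| 12 | 16.4 | 2.9 | 17.6% | 4.4% |

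The lower bound outside the window is then about 82% to 85%, and about 96% with an even spread.

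**With the TIC-P also at T1 and T2.** Windows: months 0–3, 9–12 and 21–24, so 9/24 = 37.5% observed. The other 15 months would be interpolated between measured points.

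**The case against.** The schedule is not in dispute. The objections concern what may be built on it, and four stronger readings should be set aside.

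- **That GOAL!'s own cost is left out.** A reader might infer this because only the TIC-P is named. The article does not say that it is the sole input or that delivery is excluded. It is a condensed account, intervention costing may sit in a fuller economic plan, and the session schedule and attendance records would allow it. The programme-cost point is therefore conditional.
- **That the ratio sets 3 months of costs against 24 months of QALYs.** Three months is what is observed. The analysis might annualise or interpolate; no rule is stated either way. The supportable criticism is that any such rule lacks data from the first 21 months.
- **That all costs have a 3-month window.** The recall period is attached to the healthcare questions. None is given for productivity loss.
- **That 90% of programme cost is missed.** The 90% is a share of contact hours. Weighting for shared group time lowers the bound, as shown above.

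It is also fair to say that costs are a secondary outcome, that the physical activity analysis is untouched, and that the planned probabilistic sensitivity analyses address parameter uncertainty. The last does not help here: those analyses supply no data for the unobserved months.

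An objection to the remedy also stands. Adding assessments partway through yields T1 and T2 costs only for later enrolees, possibly in different proportions by arm, and still leaves 15 months unobserved.

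**Conclusion.** The concern holds for healthcare use. The stated schedule observes 12.5% of follow-up after the start and none of year 1, yet the result is presented as cost-effectiveness after two years. This follows from the 3-month recall and the T0/T3 schedule, which Table 1 and the text state consistently for both arms. The direction of bias from the unobserved months is unknown.

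The programme-cost part is conditional. If the TIC-P were the only source, at least 90% of scheduled contact hours would lie outside its T3 window (about 82% or more of professional hours per participant, assuming groups of 5 to 12). Most delivery cost would then be missed and incremental cost biased in favour of GOAL!. The documents do not establish that this will happen. For productivity loss, coverage cannot be judged because the recall period is not given.

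**What to change.** 1. Give the TIC-P at the existing T1 and T2 contacts to all participants, in both arms, who have not yet passed them. Build 24-month costs from the observed windows with a stated interpolation rule. Treat missing T1 and T2 costs as dependent on enrolment date, and check the balance by arm.
2. State that GOAL! delivery cost is added to the intervention arm, calculated from the attendance and coaching records already kept.
3. State the recall period of the productivity questions.
4. If T1 and T2 collection is no longer feasible, present either healthcare costs in months 21–24 plus programme cost, or an explicitly extrapolated ratio with sensitivity analyses on year-1 costs. Do not label either as an observed two-year ratio.

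Cost: item 1 adds 14 + 11 = 25 questions at each of two contacts, some of which can be completed online, and needs an amendment. The authors already list questionnaire burden as a limitation in this population, so the burden is a real downside. The benefit shrinks with time: the Study status section expected recruitment to finish in the first half of 2025, and each T1 or T2 contact that passes is lost. Items 2 to 4 need no new participant data, only wording and analysis work.
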